**Study information**

| **Rationale** | Hip fractures are a significant health concern, particularly among the older patient population. The incidence of hip fractures is high at around 18.500 patients annually in the Netherlands and these injuries are associated with serious morbidity and mortality (1). Given the severe impact on health and the high costs associated with treatment and rehabilitation, hip fractures represent a substantial burden on healthcare systems (2).  For frail patients, especially those with multiple comorbidities and advanced age, surgical intervention may not always be the best option. Non-operative management (NOM) can be considered under certain circumstances (3). In these cases, the primary focus shifts towards improving the quality of life, particularly towards the end of life, with a significant emphasis on effective pain management (4). The goal is to alleviate pain and enhance comfort without subjecting patients to the risks associated with surgery (5).  One of the recent advancements in pain management for patients undergoing NOM of hip fractures is the pericapsular nerve group (PENG) block combined with phenol for neurolysis (6). The PENG block targets the sensory nerves around the hip joint, providing significant pain relief without affecting motor function. This preservation of motor function is crucial for maintaining the patient's comfort and ability to perform activities of daily living (ADL). This innovative approach offers a promising alternative for pain relief that reduces the reliance on opioids (7).  The use of the PENG block with phenol for neurolysis has already begun to be implemented by individual anesthesiologists, albeit in small numbers. Therefore, there is a growing need to establish a comprehensive implementation guideline and a standardized pathway to ensure consistency and high standards in the application of this technique. A standardized guideline would not only ensure homogeneity in the quality of PENG block administration but also provide clear recommendations on when it is appropriate to use this technique and when alternative approaches should be considered. |
| --- | --- |
| **Aim** | Given that the implementation of the PENG-block with phenol has already begun in a limited capacity across the Netherlands, it is crucial that any future implementation guidelines consider the current stage of this process. Notably, in current practice it is often the case that only one or two anesthesiologists within one hospital have administered the PENG-block, while their direct colleagues have refrained from its use. Therefore, the aim of this study is twofold: first, to explore and understand the expectations, experiences, and attitudes of anesthesiologists who are currently administering the PENG-block, and second, to compare these findings with the perspectives of anesthesiologists who have not yet adopted this practice. The study seeks to identify key technical and logistical factors that influence the acceptance and implementation of this pain management technique from the perspective of anesthesiologists. Hereby, the study aims to further current clinical implementation attempts and facilitate broader adoption of this technique in hospital settings. The following research question will be answered:  What barriers and facilitators do anesthesiologists-pain specialists identify in the implementation of the PENG-block regarding the use of the PENG-block with phenol for pain management in non-operative patients with proximal femur fractures?  Secondary questions include:   1. To what extend do anesthesiologists perceive the use of the PENG block with phenol as acceptable in the context of palliative care? 2. To what degree is successful implementation of the PENG block with phenol within existing palliative care practices perceived as feasible by anesthesiologists? 3. How appropriate do anesthesiologists perceive the PENG-block with phenol for managing pain in non-operatively managed hip fracture patients in palliative care? |
| **Study design** | This study employs a quantitative approach to a survey study design to provide a comprehensive understanding of anesthesiologists' experiences and perceptions regarding the use of the PENG-block with phenol in palliative care settings.  In order to comprehensively address the research questions, we have composed an implementation sciences-based model through which our research questions have been framed. *Figure 1* illustrates the combination of a determinant model as proposed by Geerligs et al. (8) with an evaluation model defined by Proctor et al. (9). In Geerligs et al.’s determinant model, the focus on the interaction between the system, staff, and intervention domains offers a framework for understanding the unique challenges and facilitators in the context of a hospital setting, making it the preferred model for this study. Additionally, Proctor et al.’s model is aimed at evaluating the implementation process through defining outcomes from three categories: implementation, service and client. This study adopts three of Proctor et al.’s implementation outcomes as thematic base of the survey questions:   - Acceptability: How well the PENG-block is received by anesthesiologists. - Feasibility: The practicality of implementing the PENG-block within the hospital setting. - Appropriateness: The perceived relevance and suitability of the PENG-block for managing pain in non-operative managed hip fracture patients.   These two models have both been used separately in a number of different implementational studies in a hospital setting, making their combination an appropriate conceptual foundation around which the survey questions will be framed.  Participants will provide informed consent prior to participation, with assurances of confidentiality and the right to withdraw from the study at any time without consequences. |
| **Study population** | Anesthesiologists-pain specialists in the Netherlands. |
| **Aimed number of participants in Amsterdam UMC** | ±15 |
| **Aimed number of participants in the Netherlands** | A total of 192 anesthesiologists-pain specialist are registered in the Netherlands. However, we expect survey participation rates of 60-70% resulting in a total of ±125 patients. |
| **Inclusion criteria** | Inclusion criteria for participants are anesthesiologists-pain specialists, regardless of their amount of experience with PENG-blocks, who are willing to consent to participate in the survey. |
| **Exclusion criteria** | Exclusion criteria are anesthesiologists-pain specialists without ability to participate in or complete the survey, or anesthesiologists (including residents and fellows) with a focus on other subspecialties. |
| **Number of participants/ sample size** | Based on a population of 192 anesthesiologists-pain specialists in the Netherlands, we expect survey participation rate of 65% which results in a total of 125 participants. |
| **Participant recruitment** | Recruitment of participants for this study will be conducted through a national PENG-consortium of which the researchers are a member. This national consortium has approximately 25 members throughout the Netherlands, all with an interest in furthering scientific and clinical impact of PENG and other non-operative palliative pain care management structures. A selection of consortium members will participate in the focus group and will be approached via email. Potential survey participants will also be recruited via email. This email will provide an introduction, online consent form for the survey and a link to the survey. After the survey has been distributed, a reminder mail will be sent after two weeks to those who have not started or completed the survey. |
| **Intervention** | The intervention in this study is an online survey that will be distributed across all anesthesiologists-pain specialists in the Netherlands. As stated above, survey questions will be categorized and divided according to the implementation outcomes acceptability, feasibility and appropriateness. While the majority of the survey questions are quantitative in nature (e.g. Likert-scale questions, close-ended questions, visual analogue scales and multiple-choice questions), at the end of each theme-specific survey item, a free-text question will be included. This final open-ended question invites participants to share any additional thoughts or topics they feel are relevant but were not addressed in the preceding survey questions.  Survey development will be performed by 3 researchers (ML, HW and HJS) and checked by 3 experts on relevance (RS and JWK). The survey will be pretested with 5 anesthesiologists-pain specialists to improve clarity.  The survey will be distributed online to all potentially eligible anesthesiologists. A distribution link will be sent by email to a survey in the digital survey system Research Survey. Potentially eligible participants will be sent a reminder 2 weeks after the initial distribution. |
| **Standard care** | Not applicable. |
| **Study endpoints** | Following the theoretical framework as illustrated in figure 1, the primary endpoint of our study consist of a number of barriers and facilitators categorized according to Geerligs et al.’s framework. Secondary endpoints include the implementation outcomes as described in the evaluation framework of Proctor et al. See T*able 1* for an explanation of how endpoints will be measurement. |

| **Implementation outcome** | **Definition Proctor et al.** | **Outcome measurement and data source** |
| --- | --- | --- |
| *Acceptability* | ‘The extent to which anesthesiologists perceive the use of the PENG block with phenol as satisfactory and agreeable in the context of palliative care.’ | Survey items assessing perceived ease of use, complexity of the technique and acceptability of the protocol, extend of administrative tasks, willingness to recommend its use, perceived benefits versus risks, patient friendliness, and acceptability on a five point Likert scale. |
| *Feasibility* | ‘The degree to which the PENG block with phenol can be successfully implemented within existing palliative care practices by anesthesiologists.’ | Survey items evaluating availability of resources, site readiness, technical skills required and availability of anesthesiologist expertise or training opportunities, fit into the overall care process, presence of established protocols and pain management strategies for non-operative management of hip fractures, the likelihood of integrating the technique into routine practice, previous experience with protocol implementation, most important perceived barriers and facilitators to influence feasibility and feasibility on a five point Likert scale. |
| *Appropriateness* | ‘The perceived relevance and suitability of the PENG block with phenol for managing pain in non-operatively managed hip fracture patients in palliative care.’ | Survey items addressing perceived quality of current evidence, patient-specific suitability, tension for change, openness to adopting new techniques and protocols, barriers and facilitator influencing appropriateness perceived as most important, appropriateness on five point Likert scale. |

**Table 1.** *Overview of implementation outcomes, its definitions and corresponding research questions, outcome measurements and data sources.*

| **Study parameters** | The following additional study parameters will be extracted:   - Demographics of the anesthesiologists-pain specialists: age, current position and role, type and size of institution; - Patient population: typical patient profile (age, gender, comorbidities) for those receiving PENG-blocks; - Professional background: frequency of dealing with palliative care patients, number of PENG-blocks performed, experience with other regional anesthesia techniques, additional training or certifications in pain management or palliative care. |
| --- | --- |
| **Statistical analysis** | The survey data will be analyzed using descriptive and inferential statistics, providing a quantifiable measure of anesthesiologists' experiences and perceptions. Survey responses will be analyzed using statistical software (SPSS, version 27; IBM Corporation) to identify trends and significant factors related to the implementation of the PENG-block. The open-ended questions that provide qualitative data will be investigated using a thematic analysis of the results. For this process, NVivo (version 12; QRS International) will be used. Triangulation will be performed using the Pillar Integration Process (PIP) technique as described by Johnson et al. (11). |
| **Burden on participants** | The burden for participants in this study involves completing the online survey, which will take approximately 15 minutes. |
| **Risk for participants** | The risks to participants are minimal. Participants are asked to share their experiences and opinions, which poses no physical risks. |
| **Benefits to participation in research** | Participation in the study provides anesthesiologists with the opportunity to contribute to the development of national guidelines for the implementation of the PENG block with phenol in palliative care settings. This can potentially improve the quality of care and pain management for non-operatively managed patients with hip fractures, benefiting the broader medical community and patient outcomes. |
| **Disadvantages to participation in research** | The main disadvantage for participants is the time commitment required to complete the survey. There are no other significant disadvantages associated with participation. |
| **Participant reimbursements** | Participants will not receive any reimbursements for participation in the study. |
| **Administrative aspects** | Based on a Data Management Plan (DMP), data and other records obtained will be handled in compliance with institutional regulations and ethical standards. To preserve participant confidentiality, data will be pseudonymized using a coding system and stored securely. Following the study's completion, the data will be kept for ten years before being safely destroyed. |
| **Publication policy and amendments** | The study's findings will be presented at relevant conferences and published in peer-reviewed medical journals. Before being put into action, any modifications to the study protocol will be sent to the METC for assessment and approval. |

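### Recruitment is said to run through a PENG consortium of about 25 interested members, which conflicts with a sample size and distribution based on all 192 pain specialists; any resulting lean could be examined only in part

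*Protocol*

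**What the plan says.** All the relevant text is in the protocol's Study information table.

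- **Participant recruitment**, on the route: "Recruitment of participants for this study will be conducted through a national PENG-consortium of which the researchers are a member".
- The same entry, on who that is: "This national consortium has approximately 25 members throughout the Netherlands, all with an interest in furthering scientific and clinical impact of PENG".
- The same entry then gives members a role of their own: "A selection of consortium members will participate in the focus group and will be approached via email". It adds that survey participants are approached by email too, with one reminder after two weeks. It does not say where the email addresses come from.
- **Number of participants/ sample size** starts from the 192 specialists in the country and draws this expectation from them: "we expect survey participation rate of 65% which results in a total of 125 participants".
- **Aimed number of participants in the Netherlands**: "we expect survey participation rates of 60-70% resulting in a total of ±125 patients" (the last word evidently means participants).
- **Intervention**: "an online survey that will be distributed across all anesthesiologists-pain specialists in the Netherlands".
- **Study parameters** lists age, position and role, institution type and size, number of PENG-blocks performed, frequency of palliative care contact, other regional techniques and extra training. Consortium membership and route of invitation are not listed.

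**The concern.** The recruitment entry and the other entries describe different populations. One is a group of about 25 people brought together by their interest in the technique. The other is the whole specialty of 192. The recruitment sentence covers participants in the study generally, not only the focus group, and the protocol gives no step that leads from the consortium to the remaining specialists.

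This matters because interest in PENG lies close to what the survey measures. Acceptability, feasibility and appropriateness are the secondary endpoints, and perceived barriers and facilitators are the primary one. The Aim entry also wants current users compared with colleagues who have not adopted the block. If the consortium were the frame or the main channel, favourable views could be over-represented and the reservations of non-adopters heard less. Without a membership item, the analyst could not separate members from the rest.

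**Working it through.** **1. The plan's own figure.** 192 × 0.65 = 124.8, rounded to 125, so the figure reproduces. The 60–70% range gives 192 × 0.60 = 115.2 and 192 × 0.70 = 134.4, centred on the same number.

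**2. The consortium as frame.** At most about 25 people could answer, or 25 × 0.65 = 16.25 at the stated participation rate. Neither is near 125. The sample size therefore presupposes the full frame, which the recruitment sentence does not describe.

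**3. Members' weight under the full frame.** Assume that all 25 members are among the 192 and that all respond. They are then 25/192 = 13.0% of the population and 25/125 = 20.0% of respondents. The other 100 respondents come from 192 − 25 = 167 non-members (100/167 = 59.9%).

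**4. Effect on an overall percentage.** Let a share *p* of members and *q* of non-members be favourable, with non-members responding independently of their view. The overstatement with *n* respondents is

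(25/n − 25/192) × (p − q).

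The protocol gives no values for *p* and *q*. Two assumed pairs show the range: 90% vs 40% and 80% vs 50%. The true national figures are then (25 × 0.9 + 167 × 0.4)/192 = 46.5% and (25 × 0.8 + 167 × 0.5)/192 = 53.9%.

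| Respondents n | n/192 | 25/n − 25/192 | 90% vs 40% | 80% vs 50% |
|---|---|---|---|---|
| 134 | 70% | 0.056 | +2.8 points | +1.7 points |
| 125 | 65% | 0.070 | +3.5 points | +2.1 points |
| 115 | 60% | 0.087 | +4.4 points | +2.6 points |
| 75 | 39% | 0.203 | +10.2 points | +6.1 points |
| 50 | 26% | 0.370 | +18.5 points | +11.1 points |

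Check at 125: (22.5 + 40)/125 = 50.0% against 46.5%, and (20 + 50)/125 = 56.0% against 53.9%.

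**5. Yardstick.** The 95% half-width for a proportion of 50% at n = 125, with finite population correction, is 1.96 × √(0.25/125 × 67/191) = 5.2 points. At the planned response, the effect of members alone is smaller than this.

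**The case against.** The strongest reply is that the surrounding text favours the full frame. Recruiting through a consortium can mean using it as a contact channel. Members are given a separate focus-group role, the Intervention entry sends the survey to the whole specialty, the sample size uses 192, and eligibility is open to any level of PENG experience. On this reading, one sentence is badly worded. That is probably what is intended, but it does not remove the conflict. The focus group appears nowhere in the design or burden entries, and email is a medium, not a sampling frame.

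Two further replies carry weight. First, a reader might infer that nothing collected would reveal a lean. The documents do not support that: number of PENG-blocks performed, institution and professional background are recorded, and the user versus non-user comparison is an explicit aim. What remains is that experience is not the same as interest. A consortium member who has not yet performed the block would count as a non-user and could tilt that group unnoticed.

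Second, the primary endpoint is a set of categorised barriers and facilitators, not a national favourability percentage, and at 125 respondents at least 100 would be non-members. That limits the harm. The point figures above apply to overall percentages on the secondary outcomes, and the loss of non-adopters' barriers is a risk, not something shown.

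**Conclusion.** The recruitment entry conflicts with the sample size and Intervention entries, and the sponsor should resolve this before invitations go out. At the planned 125 respondents, over-representation of members adds about 2 to 4 points to an overall percentage. This rests on the assumed shares, on every member being an eligible pain specialist, and on every member responding. The larger figures in the table need response rates of 39% or 26%, well below the planned 60–70%.

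A reader might go further and conclude that the results will lean towards enthusiasts. The documents do not establish this: it depends on how the consortium is actually used, and most of the text points to the full frame. Nor can about 25 out of 192 be taken as the known share of members. The count is approximate, and the protocol never says that members are all registered pain specialists.

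Severity: should-fix.

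**What to change.** - Reconcile the Participant recruitment and Intervention entries: state that survey invitations go to all 192 registered anesthesiologists-pain specialists, name the register or society list that supplies the addresses, and say that the consortium is used only for the focus group.
- Add one yes/no survey item on consortium membership to the study parameters.
- Report the response rate with 192 as the denominator.
- Present results overall, with consortium members excluded, and by PENG experience (user vs non-user).
- Weight to membership shares only if the number of members among the 192 has been confirmed.

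The cost is a wording change, one extra item in a survey of about 15 minutes, and one extra table. The frame and the membership item should be settled before distribution, because neither can be reliably recovered afterwards.

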
**
[figure not shown]
Figure 1.** *Combined model of determinant and evaluation frameworks by Geerligs et al. (8) and Proctor et al. (9). Taken from Damschröder (12).*
